## **4. Study Design**

### **4.1. Overall Design**

This is a randomized, non-blinded, controlled, adaptive, multicenter, Phase II study in subjects aged more than 18 years and in good health or stable clinical situation that have received a previous single dose of VAXZEVRIA.

This is a phase 2 adaptive trial developed for evaluating the immunogenicity of a dose of COMIRNATY after a previous single dose with VAXZEVRIA. A stratification will be made for the following factors: site of vaccination, sex and age. This protocol allows to test the immunogenicity and safety of a heterologous vaccination strategy after a single dose of VAXZEVRIA.

Subjects will be randomized to immediately receive or not dose of COMIRNATY in a proportion of 2:1.

If primary analysis at 14 days confirms the starting hypothesis, subjects randomized to no vaccination will be considered for administration of one dose of COMINARTY at day 28th according to Public Health Department of the Ministry of Health recommendations on heterologous vaccination. If vaccinated, subjects will be followed at the time points defined in the flowchart.

In case the primary analysis does not confirm the starting hypothesis, subject will be followed without administration of COMINARTY.

In case Public Health Department gave instructions to give the second dose of VAXZEVRIA to those subjects having received the first dose, subject will be followed as indicated in flowchart of Group 2.

Other heterologous vaccination strategies could be incorporated if deemed necessary for public health reasons. This could include the use of different boost strategies including those already marketed vaccines for comparative assessment of their safety and efficacy on SARS-CoV-2 and its variants.

The different intervention arms planned (and its corresponding control arm) can be carried-out in different trial sites, thus not all trial sites must participate in all arms.

#### **Selection sample:**

A multistage cluster sampling stratified by age groups will be carried out to obtain the number of subjects to be selected from the list of 400,000 subjects registered by Spanish Government as having received only the first dose of AZ vaccine. The first stage will be the autonomous community, the second the postcode and the third the hospital centre. Subjects will be selected in this last stage by systematic sampling stratified by age group (18-49, 50-59, and 60 and over years).

#### **Randomisation and blinding:**

- Randomization will be centralized, and each participant will be randomized stratified by age and centre. Randomization will be in a proportion of 2:1 (COMIRNATY:No vaccination)
- This is an open-label trial.

#### **4.2. Scientific Rationale for Study Design**

There is an urgent need to take decisions about how to proceed in those subjects having received a first dose of VAXZEVRIA during the Covid-19 vaccination campaign in Spain, after the decision taken by public health authorities put on hold the second dose of Vaxzevria. In addition, the ability to mix and match vaccines could make vaccination programmes more flexible, speeding up the process and reducing the impact of any supply-chain disruptions. At this moment no information exists on the safety and immunogenicity response for heterologous vaccination schemes. Therefore, a pragmatic trial is proposed to obtain enough information for public rapid decision making and to allow long-term evaluation on the safety and immunogenicity response after the boost dose of a mRNA vaccine (COMINARTY) in these subjects.

#### **4.3. Justification for Dose**

The dose of COMINARTY to be used for vaccination is the approved dose of this vaccine.

#### **4.4. End of Study Definition**

##### **Participant Completion**

A participant is considered to have completed the study if he/she has completed all study 1 year visits.

##### **Study completion.**

The study is considered complete when the last participant entering the trial has completed his/her last visit.

## **5. Study Population**

Adult subjects (18 years old or higher) in good health or stable clinical situation volunteering to participate in the trial will be recruited after giving informed consent.

Selection criteria for inclusion of subjects in the trial will be maintained as pragmatic as possible.

### **5.1. Inclusion Criteria**

Each potential participant must satisfy all of the following criteria to be enrolled in the study:

1. Adult subjects (18 years old) having received a prime VAXZEVRIA vaccination between 8 and 12 weeks before the screening visit.
2. Participants must provide consent indicating that he or she understands the purpose, procedures and potential risks and benefits of the study, and is willing to participate in the study.
3. Subjects in good health or stable clinical situation.
4. Participant is willing and able to adhere to the procedures specified in this protocol.

### **5.2. Exclusion criteria**

Any potential participant who meets any of the following criteria will be excluded from participating in the study:

1. Participant has a clinically significant acute illness (this does not include minor illnesses such as diarrhea or mild upper respiratory tract infection) or temperature  $\geq 38.0^{\circ}\text{C}$  within 24 hours prior to the planned dose of study vaccine.
2. Participant has a known or suspected allergy or history of anaphylaxis or other serious adverse reactions to COMIRNATY excipients.
3. Subjects with any contraindication to the administration of COMIRNATY, included pregnancy.
4. Subjects with prior documented COVID19 since VAXZEVRIA vaccination.
5. Subjects have symptoms or signs compatible with COVID19.
6. Subjects participating in a clinical trial in the last three months.
7. Any condition or situation precluding or interfering the compliance with the protocol.

## **6. Study Interventions and Concomitant Therapy**

Study intervention is defined as heterologous boosted strategy based on approved SARS-CoV-2 vaccine intended to be administered to a study participant according to this protocol.

### **6.1. Study Intervention(s) Administered**

#### **6.1.1. Intervention arms:**

Intervention arms (Group 1) will be the arm vaccinated with COMIRNATY after a previous vaccination with VAXZEVRIA between 8 and 12 weeks before the screening visit.

#### **6.1.2. Control arm:**

The control arm (Group 2) will have no vaccine administration. If primary analysis at 14 days confirms the starting hypothesis, subjects randomized to no vaccination will be considered for administration of one dose of COMINARTY at day 28th according to Public Health Department of the Ministry of Health recommendations on heterologous vaccination. If vaccinated, subjects will be followed at the time points defined in the flowchart (Group 2).

### **6.2. Preparation, Handling, Storage, and Accountability**

All study vaccine must be stored in a secured location with no access for unauthorized personnel and at controlled temperatures as indicated on the commercial labels and manufacturer instruction. If study vaccine is exposed to temperatures outside the specified temperature range, all relevant data will be sent to the manufacturer and sponsor to determine if the affected supplies can be used or will be replaced. The affected study vaccine must be quarantined and not used until further instruction from the sponsor is received.

Instructions for the preparation, handling and storage will be those described in the Product Information Sheet of COMIRNATY approved by AEMPS.

The investigator is responsible for ensuring that all study vaccine received at the site is inventoried and accounted for throughout the study. The study vaccine administered to the participant must be documented on the vaccine accountability form. All study vaccine will be stored and disposed of according to the manufacturer's instructions.

### **6.3. Measures to Minimize Bias: Randomization**

This is an open-label clinical trial.

The randomization list will be generated using software SAS 9 for Windows. The randomization list will be imported into the REDCap program so the researchers can randomize candidate subjects using an easier-to-use interface. Subjects that meet the selection criteria will be randomized in a 2:1 ratio between the two treatment groups (Intervention arm: administration of a COMINARTY boosted dose vs Control arm: no administration of boosted dose), stratifying by center, gender and age (18-49 years, 50-59 years and  $\geq 60$  years), in order to achieve balanced randomization in the two treatment groups. The assignment of treatment to each subject will be centralized, keeping the sequence hidden.

#### **6.4. Study Intervention Compliance**

This study will be conducted within hospitals. Treatment is administered at site and participants will receive study intervention directly from the investigator or designee, under medical supervision. The date and time of each dose administered in the clinic will be recorded in the source documents. Deviation(s) from the prescribed dosage regimen should be recorded. Intervention start and stop dates, will also be recorded.

#### **6.5. Concomitant Therapy**

Any medication or vaccine (including over the counter or prescription medicines and/or recreational drugs) at the time of enrolment or received during the study must be recorded along with:

- Reason for use
- Dates of administration including start and end dates
- Dosage information including dose and frequency

## **7. Discontinuation of Study Intervention and Participant Discontinuation/Withdrawal**

### **7.1. Discontinuation of Study Intervention**

This is not applicable. Intervention is a unique dose of COMIRNATY in the randomization visit.

### **7.2. Participant Discontinuation/Withdrawal from the Study**

A participant may withdraw from the study at any time at his/her own request or may be withdrawn at any time at the discretion of the investigator for safety, behavioural, or compliance reasons. This is expected to be uncommon.

When a participant withdraws before study completion, the reason for withdrawal is to be documented in the eCRF and in the source document. If the reason for withdrawal from the study is withdrawal of consent, then no additional assessments are allowed. The participant will be permanently discontinued from the study intervention and the study at that time.

If the participant withdraws consent for disclosure of future information, the sponsor may retain and continue to use any data collected before such a withdrawal of consent.

If a participant withdraws from the study, he/she may request destruction of any samples taken and not tested, and the investigator must document this in the study site records.

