| 
Primary immunogenicity endpoint:
 
 
Serological response to vaccination (antibodies against SARS-CoV-2 spike protein) as measured by immunoassay, 14 days after vaccine dose (Group 1) or randomization (Group 2) .
 
 
Secondary immunogenicity endpoint:
 
 
Serological response to vaccination (antibodies against SARS-CoV-2 spike protein) as measured by immunoassay, 28 days after vaccine dose (Group 1) or randomization (Group 2) .
 
SARS-CoV-2 neutralization as measured by virus neutralization assay, 14 and 28 days after vaccine dose (Group 1) or randomization(Group 2) .
 
Serological response to vaccination (antibodies against SARS-CoV-2 spike protein) as measured by immunoassay at 3, 6 and 12months after randomization.
 
Neutralizing antibody titers at 3, 6 and 12 months after randomization.
 
 
Secondary efficacy endpoints:
 
 
The number of participants with molecularly confirmed COVID-19.
 
Presence and severity of COVID-19 signs and symptoms as measured by Symptoms of Infection with Coronavirus-19 (SIC).
 
 
Primary safety endpoints:
 
 
Solicited local and systemic adverse events (AEs) for a period of 7 days after vaccination.
 
Unsolicited local and systemic adverse events (AEs) for a period of 28 days after vaccination
 
Serious adverse events (SAEs) throughout the study (from randomization until end of the study).
 
Medically-attended adverse events (MAAEs) from the day of vaccination until 6 months after the last vaccination.
 
Abnormal laboratory parameters at 1 month visit after COMIRNATY vaccination.
 
 |                                                                                                                                         |

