## **8. Study Assessments and Procedures**

### **General instructions**

Study procedures and their timing are summarized in Flow Chart (section 1.2). Protocol waivers or exemptions are not allowed.

Safety concerns should be discussed with the sponsor or sponsor representative immediately upon notice, to determine if the participant should continue or discontinue the study intervention.

Adherence to the study design requirements, including those specified in the flow chart, is essential and required for study conduct.

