#### **8.4.1. Time period and frequency for collecting and reporting AE and SAE information**

- All AEs and SAEs will be collected from the signing of the informed consent form (ICF) until the follow-up visit at the time points specified in the Flowchart.
- All AEs and SAEs that are related to investigational products will be recorded from the time of ICF signing to end of study or early study discontinuation.
- Any clinically relevant event that occurs between signing of the ICF and the first vaccination will be collected and reported as pre-existing medical condition.
- All information on AEs (non-serious and serious) and pregnancies should be recorded on the appropriate eCRF (eCRF completion will be detailed into eCRF user manual).
- All AEs will be monitored until resolution or clinical stabilization.
- SAE information will be transmitted using a SAE form. The form should be reviewed and signed by an investigator and must be transmitted within 24 hours from initiation of SAE.
- All events that meet the definition of a SAE will be reported as SAEs, regardless of whether they are protocol-specific assessments.

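### Investigator-initiated withdrawal can end safety recording before the SAE and MAAE endpoint windows close, although the Group 1 dose has already been given

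*Protocol*

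**What the plan says.** Four parts of the protocol bear on this.

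- **Withdrawal.** Section 7.2, headed "Participant Discontinuation/Withdrawal from the Study", says that a participant "may be withdrawn at any time at the discretion of the investigator for safety, behavioural, or compliance reasons". It adds: "This is expected to be uncommon". It rules out further assessments only where the reason is withdrawal of consent.
- **Intervention.** Section 7.1, on stopping the intervention, reads: "This is not applicable. Intervention is a unique dose of COMIRNATY in the randomization visit". The general instructions of section 8 nevertheless send safety concerns to the sponsor "to determine if the participant should continue or discontinue the study intervention". Section 6.1.2 allows a Group 2 dose at day 28.
- **Recording.** Under section 8.4.1, product-related AEs and SAEs "will be recorded from the time of ICF signing to end of study or early study discontinuation". The same list says: "All AEs will be monitored until resolution or clinical stabilization".
- **Endpoints.** The synopsis lists as a primary safety endpoint "Serious adverse events (SAEs) throughout the study (from randomization until end of the study". It also lists MAAEs up to 6 months after the last vaccination. Table 3.1 repeats both windows, and the synopsis plans one year of follow-up for each participant.

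**The concern.** In many trials, withdrawal for safety at least stops further exposure. Here a Group 1 participant has had the whole intervention by the end of Visit 1. Taking that person out of the study afterwards undoes nothing and removes only the observation.

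One of the named grounds is safety, so those removed are likely to differ from the rest in their risk of later events. If recording ends with their participation, the later SAEs, MAAEs and antibody results are lost selectively. For the safety endpoints the expected direction is under-counting. No analysis plan can restore this: the protocol's main data set is all observed data (DPS1, section 9.2), and events never recorded are not observed.

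**Working it through.** The protocol states no figure on this point, so the check sets the sections side by side and then illustrates the size under assumptions.

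**1. What is collected after an investigator-initiated withdrawal?**

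| Item | Window required | Recording rule after withdrawal |
|---|---|---|
| SAE endpoint (1.1, Table 3.1) | Randomization to end of study | Related events: to early study discontinuation (8.4.1) |
| MAAE endpoint (1.1, Table 3.1) | Vaccination to 6 months after the last vaccination | No separate rule; asked about at study visits (section 8) |
| Event already recorded | Not applicable | Monitored to resolution or stabilization (8.4.1) |
| New event, any cause | As for SAE and MAAE above | To the follow-up visit at flowchart time points (8.4.1), visits that a withdrawn participant may no longer attend |
| Titres at 3, 6 and 12 months | Scheduled sampling | Not stated |

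No section requires new events or later samples to be collected from a participant whom the investigator has withdrawn. For related events, the text points to a stop.

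**2. How much follow-up is at stake for one person?** The last visit is at day 360. A Group 1 participant withdrawn at the day-28 visit loses up to 360 − 28 = 332 days of SAE follow-up, about 11 months. With 6 months taken as 180 days, the loss of MAAE follow-up is up to 180 − 28 = 152 days. Later withdrawal loses less.

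**3. How large could the under-count be?** Let w be the share of Group 1 withdrawn, p the risk of a later SAE in those who stay, and RR the risk ratio in those withdrawn. All withdrawals are taken as early, and no later event in those withdrawn is recorded.

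- Recorded risk = (1 − w)p
- True risk = (1 − w)p + w·p·RR
- Share missed = w·RR / [(1 − w) + w·RR], in which p cancels

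Example with w = 2% and RR = 5: 0.10 / (0.98 + 0.10) = 9.3%.

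| w (of 400) | RR 1 | RR 5 | RR 10 |
|---|---|---|---|
| 1% (4) | 1.0% | 4.8% | 9.2% |
| 2% (8) | 2.0% | 9.3% | 16.9% |
| 5% (20) | 5.0% | 20.8% | 34.5% |

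In counts, with an assumed p of 1%: at w = 2% and RR = 5, 400 × 0.02 × 0.05 = 0.4 of 400 × 0.0108 = 4.32 expected SAEs go unrecorded. At the far corner (w = 5%, RR = 10) it is 400 × 0.05 × 0.10 = 2 of 400 × 0.0145 = 5.8. The values of w, RR and p are all assumptions.

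**4. Is section 7.1 consistent with the rest?** It calls discontinuation of intervention inapplicable and places the only dose at randomization. Section 8 provides for a decision to continue or discontinue the intervention. Section 9.3.5 counts SAEs leading to treatment discontinuation. DPS2 in section 9.2 drops observations after discontinuation. Section 6.1.2 allows a Group 2 dose at day 28. These do not fit together.

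**The case against.** The case for leaving the text alone has real substance. The event that leads to a safety withdrawal has been recorded and is followed to resolution, so it counts in the safety tables. The bar on further assessments in 7.2 is tied to withdrawal of consent, so the protocol does not forbid continued follow-up of others. The first item of 8.4.1 collects all AEs without an early cut-off. Monitoring known events to resolution and recording new ones to discontinuation can also both apply, so 8.4.1 is loosely worded rather than plainly self-contradictory. Withdrawals are expected to be rare. All of this stands and limits the point to new events and later titres. It does not remove the point, because the absence of a bar is not a duty to continue.

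A reader might infer more than the protocol supports:

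- **That the worst events disappear.** They do not; only events after the withdrawal are at risk.
- **That controls vaccinated elsewhere would be removed for non-compliance.** No section calls outside vaccination a compliance breach. Section 6.5 requires vaccines received during the study to be recorded. Sections 1.1 and 4.1 continue follow-up if the authorities direct a second VAXZEVRIA dose.
- **That 7.2 destroys the long-term randomized comparison.** The possible day-28 dose for controls may end that comparison by design.
- **That safety should be struck out as a ground for withdrawal.** That ground protects participants, and the data problem can be solved without touching it.

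**Conclusion.** The point holds in a limited form. Section 7.2 together with 8.4.1 allows recording to stop earlier than the primary safety endpoints require, and one of the triggers is safety itself. In Group 1 the withdrawal brings no reduction in exposure in return. In Group 2 this applies only after a day-28 dose, if one is given.

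The likely effect is small in number. Under the assumed 1 to 5% withdrawn it runs from 1% of later SAEs missed, if withdrawal is unrelated to risk, to about a third at the extreme. It runs towards under-counting when withdrawal is for safety. That the loss is selective is an inference from the named grounds, not something the protocol states. The day-14 primary comparison is little affected, because it falls two weeks after randomization. The change is worth making because uncollected data cannot be recovered later.

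**What to change.** 1. **Section 7.2.** Keep the grounds for investigator-initiated withdrawal. Add that a participant discontinued by the investigator, or with a protocol deviation, an outside vaccination or an AE, remains in SAE/MAAE collection and scheduled immunogenicity sampling unless consent is withdrawn.
2. **Section 8.4.1.** Replace the stop at early study discontinuation with withdrawal of consent, so that recording agrees with the endpoint windows in the synopsis and Table 3.1.
3. **Section 7.1.** Reconcile it with the section 8 general instructions, with the discontinuation terms in 9.2 and 9.3.5, and with the possible Group 2 dose at day 28. Which clinical rule applies is for the sponsor to settle.

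This is a wording amendment. The visits and samples are already planned for every participant. The downside is that sites go on following a few discontinued participants.

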### **7.3. Lost to Follow-Up**

To reduce the chances of a participant being deemed lost to follow-up, prior to randomization attempts should be made to obtain contact information from each participant, eg, home, work, and mobile telephone numbers and email addresses for both the participant as well as appropriate family members.

A participant will be considered lost to follow-up if he/she is unreachable for the study site per telephone directly to the patient or relatives (for at least in two occasions), or by written correspondence. A participant cannot be deemed lost to follow-up until all reasonable efforts made by the study-site personnel to contact the participant are deemed futile.

## **8. Study Assessments and Procedures**

### **General instructions**

Study procedures and their timing are summarized in Flow Chart (section 1.2). Protocol waivers or exemptions are not allowed.

Safety concerns should be discussed with the sponsor or sponsor representative immediately upon notice, to determine if the participant should continue or discontinue the study intervention.

Adherence to the study design requirements, including those specified in the flow chart, is essential and required for study conduct.

### **Screening visit**

Screening for eligible participants will be performed within  $\leq 7$  days before randomization. The inclusion and exclusion criteria for enrolling participants in this study are described in section 5. If there is a question about these criteria, the investigator must consult with the sponsor (instituto de Salud Carlos III) representative and resolve any issues before enrolling a participant in the study. Waivers are not allowed.

The study will be explained to the participant and informed consent will be obtained prior to any study procedure.

After screening and obtaining informed consent, the following procedures will be performed:

- Record demographic information.
- Record medical history.
- Record concomitant medications and vaccinations if taken within 6 months prior to enrolment in this trial.
- Perform a complete physical examination, including height and weight.
- Measure vital signs (body temperature, pulse, blood pressure).
- Pregnancy test

